### AE reporting

AEs, adverse reactions (ARs), serious AE/ARs (SAEs/SARs) and suspected unexpected SARs will be defined as per the International Conference on Harmonisation definitions. A suitably qualified medical doctor will determine the relationship and causality of each AE to the study drug as either ‘related’ (defined as having a plausible temporal relation and not judged attributable to other causes) or ‘not related’. They will also make an assessment on severity and seriousness. Abnormal or significant changes in laboratory results are only AEs if they are deemed to be of clinical significance or if a medical intervention is required. Whether a patient needs to be withdrawn due to the severity of their AE is left up to the discretion of principal investigator.

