### Stopping criteria

Dose-escalation stopping criteria will be met if two patients within a trial group experience any combination of: a SAE defined as possibly, probably or definitely related to the trial drug (ie, it is a SAR), an adverse event that is severe and at least possibly related to the trial drug or any of the objective stopping criteria detailed box 1. The following will then occur:Box 1Objective stopping criteria triggering a Data Monitoring Committee safety review of dose escalationQTcB >500 ms (or >530 ms if baseline QTcB=450–480 ms) OR QTcB change from baseline >60 ms (based on an average of triplicate electrocardiogram (ECGs)).Acute pulmonary oedema or congestive heart failure.Symptomatic systolic BP <90 mm Hg and/or diastolic blood pressure (BP) <60 mm Hg OR persistent symptomatic systolic BP 80–90 mm Hg for >15 mins OR severe hypertension (as defined by BP >180/120 mm Hg).ST-elevation myocardial infarction (STEMI) occurrenceAtrial fibrillation with rapid ventricular response >150/min, supraventricular tachycardia or bradycardia that requires treatment or is recurrent or persistent.Sustained ventricular tachycardia or ventricular fibrillation.Any patient who develops doubling of creatinine.Systemic hypersensitivity reaction that cannot be attributed to an identifiable cause.If a life-threatening infection is confirmed clinically with a positive microbiological test.Signs suggestive of hepatic failure including encephalopathy, increasing ascites, signs of coagulopathy, liver pain and/or tenderness on palpation, hypoglycaemia presumed to be secondary to liver failure and active GI bleeding. Withdrawal also if alanine aminotransferase (ALT)>3 ULN.Seizure activity, coma, severe lethargy or somnolence.Risk of respiratory insufficiency requiring intubation.

Dosing will be immediately discontinued for the patients experiencing the event.Dosing will be halted for all other patients currently in the treatment period of the trial (ie, patients receiving treatment in the same group).A safety review by the independent DMC will be conducted to determine how to proceed with the trial.Any further single instances of the events outlined above for the same group will trigger a further DMC safety review.Any patients who have their dosing discontinued will be withdrawn from the trial.

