Additionally, specific objective stopping criteria are set out in box 1, which may trigger an unscheduled DMC review prior to any further dose escalations. Specific and general withdrawal criteria are also listed in online supplementary file 1.

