### Safety monitoring committees

The TMG and the DMC are independent of each other. The function of the DMC is delineated in the DMC charter (online supplementary file 2). The chief investigator of the trial will report to the DMC on the course of the trial during open sessions of the DMC. All DMC meetings will be held in private without any involvement of the trial team. The unblinded statistician is the only person who reports to the DMC and is part of the TMG. However, any data presented to the TMG are presented in a manner that maintains the blind.

The TMG will assess safety in a blinded manner on an ongoing basis at regular intervals during the course of the trial. Between part A and part B, the DMC will be formally convened to review the unblinded data with the unblinded statistician to determine whether it is reasonable for the trial to progress to the next stage.

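### Box 1 omits death, so a death without another Box 1 event counts towards the two-patient halt only after a causality call that the article words in two ways

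*Protocol article*

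**What the plan says.** All references are to the protocol article.

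- **Stopping criteria.** The halt is met when two patients in a trial group have any combination of three things: an SAE meeting "a SAE defined as possibly, probably or definitely related to the trial drug" (glossed as a SAR), a severe adverse event that is at least possibly related, or any Box 1 item. Dosing in the group is then halted and the independent DMC reviews safety. After that, "Any further single instances of the events outlined above for the same group will trigger a further DMC safety review".
- **Box 1.** It covers QTcB, pulmonary oedema or heart failure, blood pressure, "ST-elevation myocardial infarction (STEMI"), supraventricular and ventricular arrhythmia, "Any patient who develops doubling of creatinine", hypersensitivity, life-threatening infection, hepatic failure or raised ALT, seizure or coma, and respiratory insufficiency. Only the hypersensitivity item carries an attribution test of its own. Death does not appear.
- **Paragraph after Box 1.** It describes the Box 1 criteria as ones "which may trigger an unscheduled DMC review prior to any further dose escalations".
- **AE reporting.** A doctor rates each event as related, meaning "having a plausible temporal relation and not judged attributable to other causes", or as not related. There are no intermediate grades.
- **Safety monitoring committees.** "The TMG will assess safety in a blinded manner on an ongoing basis at regular intervals". "Between part A and part B, the DMC will be formally convened to review the unblinded data with the unblinded statistician".

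**The concern.** Box 1 exists so that some events count towards the halt without anyone having to decide what caused them. A QTcB change above 60 ms has that status and death does not. Every participant has coronary disease, so a cardiac death will nearly always have an explanation other than the drug. The Background also notes that IL-2 is contraindicated in severe cardiac disease.

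A death put down to underlying disease could therefore leave the count at zero. The mandatory halt and the unblinded DMC review attached to it would then not be triggered. What remains mandatory is TMG review, which is blinded and uses aggregated data. The only scheduled unblinded review that the article describes falls between Parts A and B.

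**Working it through.** **1. Inputs.** Part A has five groups of 5 and Part B has four groups of 8. 5×5 + 4×8 = 57, which matches the stated sample size. The halt threshold is two patients per group. The article gives no event rates, so those used in step 4 are assumptions.

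**2. The two causality wordings side by side.**

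| Place | Scale | What lets an event count |
|---|---|---|
| Stopping criteria | possibly / probably / definitely | at least possibly related |
| AE reporting | related / not related | plausible timing and not judged attributable to another cause |

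Take a death that could be due to the drug or to coronary disease. Under Stopping criteria it is at least possibly related, so it counts. Under AE reporting the answer depends on the assessor. If the other cause has not been positively identified, the event can be called related. If the assessor regards coronary disease as the explanation, it is not related and does not count. The SAR gloss suggests that the three grades are meant to collapse into related. The article does not say so outright, and no equivalent gloss is attached to the severe-AE route.

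**3. Counting under the rule as printed.**

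- Two deaths in one group, both called not related, with no Box 1 event: 0 + 0 = 0, below 2, so no mandatory halt. With death in Box 1: 1 + 1 = 2, so the halt applies.
- One such death plus one QTcB change above 60 ms in another patient: 0 + 1 = 1, so no mandatory halt. The paragraph after Box 1 does allow an unscheduled DMC review on the QTcB event. With death in Box 1: 1 + 1 = 2.

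**4. What adding death would cost in extra pauses.** Let p be the share of patients with a death that would newly count, and q the share who already have a countable event. Events are assumed independent.

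- Combined risk: u = 1 − (1 − p)(1 − q).
- Extra first trigger per group of n: E = P(Bin(n, u) ≥ 2) − P(Bin(n, q) ≥ 2).
- Over g groups: 1 − (1 − E)^g.

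Example for Part B (n = 8, g = 4) with p = 1% and q = 5%: u = 1 − 0.99×0.95 = 0.0595. E = 0.07801 − 0.05724, which is 0.02076 before rounding. Over four groups, 1 − (1 − 0.02076)^4 = 0.0805.

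| Part B, death only | p = 0.25% | p = 0.5% | p = 1% |
|---|---|---|---|
| q = 0 | 0.07% | 0.27% | 1.07% |
| q = 5% | 1.97% | 3.97% | 8.05% |
| q = 10% | 2.66% | 5.29% | 10.43% |

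For Part A (n = 5, g = 5) at p = 1%, the same formula gives 0.49%, 4.31% and 6.57% for q = 0, 5% and 10%.

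The rule also calls for a further review at each later single event. Counting those, the expected number of extra reviews is g × (E[max(X_u − 1, 0)] − E[max(X_q − 1, 0)]). For Part B at q = 5% this is 0.02, 0.05 and 0.10 at the three values of p.

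Most extra triggers in the q = 5% row pair a death with an event that already counts. Those with no such event in the group have probability 0.95^8 × P(Bin(8, p) ≥ 2). At p = 1% this is 0.6634×0.00269 = 0.0018, or 9% of E. At p = 0.25% it is 0.6634×0.000173 = 0.00011, or 2% of E.

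**The case against.** - **The causality wordings may not conflict.** An event that could be due to either cause has not been judged attributable to the other one, and the SAR gloss nearly equates the grades with related. This largely stands for SAEs. A reader might infer a flat contradiction, but the text supports only an ambiguity that two careful assessors could resolve differently.
- **Many deaths would count anyway.** Ventricular fibrillation, STEMI, pulmonary oedema and symptomatic hypotension are in Box 1. This stands, and the gap is limited to deaths with no such event, for example an unwitnessed one.
- **Deaths would not go unseen.** Sentinel dosing with safety review, TMG review of events and records before each dose decision, and the escalation cap all remain. A single Box 1 event may also open a DMC review. A reader might infer that deaths could pass without any review, and the article does not support that. These safeguards are either blinded or discretionary, however, and none is a defined trigger for death.
- **The charter and supplementary file 1 may cover deaths.** They are not shown, so this cannot be excluded. It limits the size of the finding but does not resolve the wording in the article.
- **Non-ST-elevation infarction.** A reader might also infer that listing only STEMI is a defect. In Part B, telling a new non-ST-elevation infarction from the index event is a matter of judgement, so leaving it off an objective list is defensible. In Part A, study troponin is scheduled only at V2, V7 and V8, so a wider item would lean on unscheduled diagnosis. No change to the infarction item is proposed.

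**Conclusion.** The point holds as a cheap improvement to a safety rule. As printed, Box 1 gives automatic weight to laboratory and ECG findings but not to death. A death outside the Box 1 mechanisms depends on a causality call whose threshold is worded in two ways. Two such deaths in one group, both called not related, would leave the mandatory halt untriggered. That conclusion is logical and needs no event rate.

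The percentages above measure the cost of the remedy under assumed, independent event rates. They should not be read as the probability of missed harm, which the article gives no basis to estimate. The verdict also assumes that the unseen charter and supplementary file 1 do not already make death a trigger.

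**What to change.** 1. Add death from any cause to Box 1, for both parts.
2. State in Stopping criteria that at-least-possibly-related is the threshold for the rule, and that the mere presence of coronary disease as an alternative explanation does not make an event not related. Align the scale in AE reporting with this.

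The change is one line in Box 1, one sentence on causality and an aligned scale. The trial began in May 2017, so it needs an amendment. The statistical cost is the small chance of extra DMC pauses shown in the working, and each trigger leads to a pause and review, not to termination. If the DMC charter or supplementary file 1 already treats death as a trigger, Box 1 need only be made to match.

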**Figure 1 F1:**
[figure not shown]
Trial design per patient. Each patient will make a total of eight study visits. IL-2, interleukin; V, visit.

There are two follow-up visits (V7 and V8). Assessments during both visits will include a medical review, physical examination, vitals, ECGs and safety bloods tests. Additionally, at V8, a follow-up thyroid function blood test and echocardiogram will be performed.

In addition, during visits V2 and V7 (figure 1), cardiac biomarkers (high sensitivity C reactive protein (hs-CRP), IL-6, brain-type natriuretic peptide (BNP) and troponin) and lymphocyte subsets (including Treg level, see below) analysis will be performed. During visit V8, cardiac biomarkers will be reaassessed.

A total of 25 patients, five in each of the five dosing groups, will be included in part A (drug:placebo ratio of 3:2). In line with current phase I trial designs, a sentinel dosing approach will be employed whereby the first two patients of each group will be allocated to either aldesleukin or placebo in a random order. After a blinded safety review of these first two patients, the remaining patients will then be dosed (see figure 2).

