### Outcome measure

#### Part A

The primary outcome will be the safety of IL-2 in patients. This will be assessed through:A review of AEs and SAEs, and concomitant medications.Changes in safety bloods (electrolytes (sodium, potassium and urea), bone profile (calcium and phosphate), serum creatinine, liver function tests (alanine transaminase, aspartate transaminase, alkaline phosphatase, bilirubin and gamma glutamyl transferase (GT)), thyroid function tests (thyroid stimulating hormone), blood glucose, full blood count and differential, and clotting (prothrombin time and activated partial thromboplastin time).Twelve-lead ECG and cardiac monitoring changes (arrhythmias, ischaemic changes and QTcB).Vital observations (blood pressure, heart rate, respiratory rate, peripheral oxygen saturation and temperature).Echocardiogram changes at baseline and follow-up.

Exploratory endpoints will include:Change in the mean circulating Treg level measured by fluorescence activated cell sorting (FACS) analysis following treatment with IL-2, over the 5 days of the treatment period.Change in cardiac biomarker measurements including hs-CRP, troponin I, IL-6 and b-type natriuretic peptide) from analysed blood samples.Change in lymphocyte subsets measured by FACS analysis.Pharmacokinetic analysis of IL-2 levels.

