#### Part B

As with part A, the primary endpoint will be safety and tolerability of IL-2. A further primary endpoint will be the change in mean circulating Treg levels and whether IL-2 increases mean circulating Treg levels by at least 75% over the 5 days of the treatment period. Exploratory endpoints are the same as for Part A.

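### Patients whose dosing is discontinued are also withdrawn from the trial, so post-treatment safety and Treg data are lost selectively after toxicity

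*Protocol article*

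**What the plan says.** All references are to the protocol article.

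**The rule.** Stopping criteria opens with a group-level trigger: "Dose-escalation stopping criteria will be met if two patients within a trial group experience any combination of" a related serious event, a severe and at least possibly related event, or a Box 1 criterion. A list of consequences follows. For those who had the event: "Dosing will be immediately discontinued for the patients experiencing the event". For the rest of the group: "Dosing will be halted for all other patients currently in the treatment period of the trial". The independent DMC then reviews safety and decides how to go on. The list ends: "Any patients who have their dosing discontinued will be withdrawn from the trial". No exception is given.

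**The outcomes.** For part A, Outcome measure says "The primary outcome will be the safety of IL-2 in patients" and lists among its components "Echocardiogram changes at baseline and follow-up". For part B, "the primary endpoint will be safety and tolerability of IL-2", and a further primary endpoint is whether mean circulating Treg rises by at least 75% over the treatment period.

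**The visits.** Under Study protocol, Part A, dosing takes place at V2 to V6 and follow-up at V7 and V8. Both follow-up visits include examination, vital signs, ECGs and safety bloods. In addition, "at V8, a follow-up thyroid function blood test and echocardiogram will be performed". Lymphocyte subsets, including Treg, are measured at V2 and V7. Part B uses the same schedule.

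**Withdrawal elsewhere.** AE reporting leaves withdrawal for the severity of an adverse event to the principal investigator. Stopping criteria refers to supplementary file 1, which is not shown, for specific and general withdrawal criteria.

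**The concern.** Stopping a drug and leaving a trial are different events, and the rule treats them as one. A patient discontinued between V2 and V6 for, say, pulmonary oedema or a doubled creatinine (both in Box 1) would have no scheduled follow-up echocardiogram, and no V7 or V8 creatinine, ECG or vital signs. Whether such an injury resolves is a central safety question in a population for which the Background says the drug is contraindicated when cardiac disease is severe.

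The missing data would not be missing at random. Patients are removed because of a safety event, and what is then missing is later safety information on the same patients. With three or six treated patients per dose, one or two such losses change what the follow-up summaries describe.

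The same withdrawal removes the V7 Treg value. In part B that is the only post-treatment measurement for a primary endpoint, and the Background says the part B Treg data will help select a dose for later trials in acute coronary syndrome.

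**Working it through.** **1. Plan's own figure.** Part A: 5 groups × 5 = 25. Part B: 4 groups × 8 = 32. Total 25 + 32 = 57, as stated in Statistical methods. The ratios of 3:2 and 6:2 give 5 × 3 + 4 × 6 = 39 active and 5 × 2 + 4 × 2 = 18 placebo. The article has no power calculation to reproduce.

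**2. What is lost on discontinuation during V2 to V6.**

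| Data | When collected | After withdrawal under the rule |
|---|---|---|
| Triggering event, adverse events to date | As they occur | Kept |
| Safety bloods, ECG, vital signs during treatment | V2 to V6 | Kept up to withdrawal |
| Post-treatment bloods, ECG, vital signs | V7, V8 | Lost |
| Follow-up echocardiogram, thyroid test | V8 | Lost |
| Post-treatment Treg | V7 | Lost |

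**3. Size at the two-patient trigger.** Share of a dose group's active patients lost to follow-up = k/n, where k is the number of withdrawn patients on active drug and n is 3 (part A) or 6 (part B). Each group also has two placebo patients, so k can be 0, 1 or 2.

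| Trigger patients on active drug | Part A | Part B |
|---|---|---|
| Both | 2/3 = 67% (1 left) | 2/6 = 33% (4 left) |
| One | 1/3 = 33% (2 left) | 1/6 = 17% (5 left) |
| None | 0 | 0 |

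Whatever the allocation, two withdrawals are 2/5 = 40% of all patients in a part A group and 2/8 = 25% in a part B group.

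**4. Size for a single discontinuation.** If the sentence also applies outside the two-patient trigger, one discontinuation costs at most 1/3 = 33% or 1/6 = 17% of a dose's active follow-up.

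**5. How often.** The article gives no event rate, so the rates here are assumptions. With independent events at rate p per active patient, P(at least 1) = 1 − (1 − p)^n and P(at least 2) = 1 − (1 − p)^n − np(1 − p)^(n−1).

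| Assumed p | At least 1, A (n = 3) | At least 1, B (n = 6) | At least 2, A | At least 2, B |
|---|---|---|---|---|
| 5% | 14.3% | 26.5% | 0.7% | 3.3% |
| 10% | 27.1% | 46.9% | 2.8% | 11.4% |
| 20% | 48.8% | 73.8% | 10.4% | 34.5% |
| 30% | 65.7% | 88.2% | 21.6% | 58.0% |

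These are probabilities per dose group. At low rates the two-patient case is uncommon, but it is most likely at the doses where follow-up matters most.

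**6. After the fix.** If stopping drug does not end follow-up, this rule causes no loss in any group, and the total stays at 57.

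**The case against.** Several limits are fair, and three stronger readings do not survive them.

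- *A reader might infer that bloods, ECG and vital signs are seen only at V7 and V8.* They are not. Study protocol, Part A schedules them at every dosing visit, with cardiac monitoring before and after each dose. Only their post-treatment values are at stake, together with the V8 echocardiogram and thyroid test and the V7 Treg sample.
- *A reader might infer that a toxic dose would look clean and be taken forward unnoticed.* The article does not support that. The triggering event is itself primary safety data, adverse events are summarised by dose, the TMG reviews safety data before each dose decision, and two qualifying events send the trial to the DMC. What is lost is the later course of the event and the Treg response.
- *A reader might infer that the other patients in the group are withdrawn too.* The article uses *discontinued* for patients with the event and *halted* for the rest, and ties withdrawal only to the first. Halted patients await the DMC's decision.

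Two further points stand. The sentence closes a list that follows the two-patient trigger, so its reach to a single event rests on its general wording. Supplementary file 1 or the full protocol may provide for follow-up after withdrawal.

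None of this removes the point. The article does not merely leave follow-up unmentioned. It states a rule that, if followed, ends it. If another document says otherwise, the two conflict and must be reconciled.

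A last objection is that keeping partly dosed patients mixes exposures in the Treg summaries. That is true, and reporting the number of doses received lets a reader see it.

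**Conclusion.** The concern holds in limited form. Read as written, the rule makes discontinuation of dosing end follow-up, and so removes post-treatment primary-outcome data selectively in patients with toxicity: bloods, ECG and vital signs at V7 and V8, the echocardiogram and thyroid test at V8, and the V7 Treg value. Events and measurements up to withdrawal are kept and reviewed.

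The percentages are maximums: 67% (part A) or 33% (part B) of a dose's active patients at the two-patient trigger, assuming both are on active drug, and 33% or 17% for one discontinuation, assuming that the sentence reaches single events and the patient is on active drug. The conclusion also assumes that the unseen documents do not already keep these patients in follow-up.

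**What to change.** Replace the sentence with one to this effect: patients whose dosing is discontinued are withdrawn from study drug only and, unless they withdraw consent, remain in the trial for the scheduled V7 and V8 assessments.

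For the analysis, include them in the safety summaries of their assigned dose group, and report their Treg values with the number of doses received. Reconcile the new sentence with the withdrawal criteria in supplementary file 1. Leave every dosing, halting and stopping rule as it stands. The change concerns data collection only.

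The cost is small. It takes about one sentence in the protocol, and the visits are already in the schedule. The downside is follow-up visits for patients no longer on drug, and Treg summaries that include some partly dosed patients.
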